**Figure 1 Flowchart for anxiety**

EXCLUSION

bCBT (N=78)

Duration: 12-20 weeks

CBTAU (N=78)

Duration: 12-20 weeks

WEEK 64-72 (T3)

WEEK 12-20 (T2)

WEEK 6-10 (T1)

WEEK 1: BASELINE (T0)

RANDOMIZATION (N=156)

ASSESSMENT OF ELIGIBILITY

ENROLLMENT

# STUDY POPULATION

## Population (base)

## The study targets adults with a current severe anxiety disorder (panic disorder with or without agoraphobia, social phobia, and generalized anxiety disorder), who were referred to and enrolled in an outpatient treatment in specialized mental healthcare center of GGZ Altrecht, GGZ inGeest or GGZ Oost Brabant. The likelihood that the planned number of patients can be recruited from the defined source population is considered high. Recruitment will take place during a time span of 18 months (see flowchart). Recruitment will start at the outpatients departments of GGZingeest ‘De Nieuwe Valerius’, at both outpatient departments of GGZ Altrecht and GGZ Oost-Brabant location Oss. Based on the number of patients that were diagnosed with an anxiety disorder at GGZinGeest last year we would expect around 30 patients per month receiving treatment. We aim to include 8-10 patients per month in the current study. If after 6 months the number of included patients is less than 78 patients, the management of GGZ inGeest has agreed to add two more locations as recruitment sites for this study, yielding a total of approximately 800 patients from which to recruit the intended 156 study participants

## Inclusion criteria

In order to be eligible to participate in this study, a patient must meet all of the following criteria:

- 18 years or older;

- meet the criteria for a severe anxiety disorder (social phobia, panic disorder with or without agoraphobia and generalized anxiety disorder), as determined by a structured interview (SICD-I)

- have sufficient command of the Dutch language, both verbal and written;

- have access to the Internet, an e-mail address and a (tablet) computer;

- are willing to be randomly allocated to on of the two treatments;

- provide signed informed consent.

## Exclusion criteria

A potential subject who meets any of the following criteria will be excluded from participation in this study:

-Primary diagnosis of a bipolar, psychotic or substance abuse disorder and/or acute risk of suicide

-Use of psychotropic medication is not an exclusion criterion

## Sample size calculation

In economic evaluations we are calculating the power to estimate the joint distribution of costs and treatment effects. Subsequently, we need more information for estimating power compared to clinical trials, namely expected costs of treatments, expected covariance of treatment effects/costs, and the maximum willingness to pay for the treatment effect. To incorporate this information, the formula of Glick et al. (2011) can be used. A goal of sample size and power calculation for cost-effectiveness analysis is to identify the likelihood that an experiment will allow us to be confident that a therapy is acceptable or not when we adopt a particular willingness to pay.

For this study a sample size of 156 is based on a formula to estimate the power of a cost-effectiveness analyses. (Glick, 2011)

$$n=\frac{{2(z_{\alpha}+z_{\beta)}}^{2}\left( {sd}^{2}+\left( W^{2}{sd}^{2} \right)-\left( 2W\rho{sd}_{c}{sd}_{q} \right) \right)}{\left( WE-C \right)^{2}}$$

$$n=sample size/group$$

$$z_{\alpha}=z statistics for alpha$$

$$z_{\beta}=z statistics for Beta$$

$${sd}_{c}=Expected standard deviation costs$$

$${sd}_{e}=Expected standard deviation effects$$

$$W=Willingness to pay$$

$$C=Expected differences in costs$$

$$E=Expected differences in effects$$

$$\rho=correlation between differences in costs and effects$$

($z_{\alpha}=1,96$, $z_{\beta}=0,84$,${sd}_{c}=800$, ${sd}_{e}=0,02$, $W=80,000, C=832,E=0,02 \rho=0,1)$

Following the formula, we may expect that the point estimate for the cost-effectiveness ratio will be around 40,000 per quality- adjusted life year (QALY), using only a small increase in quality of life and lower costs for blended eHealth, we want to design an experiment that will provide an 80% chance (i.e., power) to be 95% confident that the therapy is good value when we are willing to pay at most 80,000 per QALY. In the Netherlands, a costs-effectiveness ratio between 20.000 and 80.000 Euro per QALY is assumed acceptable.

Glick, H.A. (2011). Sample size and power for cost-effectiveness analysis (part 1). Pharmacoeconomics, 29 (3), 189-198.

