# STUDY DESIGN

The study is a cost-effectiveness study, designed as a parallel-group randomized controlled trial (N = 156), in which participants are randomly allocated to either bCBT (n=78) or CBT-TAU (n=78). Participants are recruited in Dutch specialized mental healthcare centers (GGZInGeest, GGZAltrecht or GGZ Oost Brabant), large scale mental health service organizations, respectively in the Amsterdam, Utrecht and Noord-Brabant region.

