#### Process data

Data for process analyses are obtained from the administration of the participating mental health care institutions and through usage statistics of the online platform. We will consider the following aspects:

**Recruitment**: how much time is required for the recruitment of patients?

**Treatment adherence**: What is the percentage of dropout during therapy, when do patients drop out (number of completed sessions)? What is the reason for treatment dropout? Number of face-to-face contacts and number of cancellations. Do patients complete homework exercises?

**Time investment**: By both the patient and the therapist.

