## Withdrawal of individual subjects

Subjects can leave the study at any time for any reason if they wish to do so without any consequences. The investigator can decide to withdraw a subject from the study for urgent medical reasons.

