## Replacement of individual subjects after withdrawal

Not applicable.

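### The 156 patients randomised are exactly what the power formula needs with complete data, so the stated 80% power makes no allowance for attrition to weeks 64-72

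*Protocol*

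**What the plan says.** Section 4.4 (Sample size calculation) attributes the total to a net-benefit power formula: "For this study a sample size of 156 is based on a formula to estimate the power of a cost-effectiveness analyses". It defines the result per arm, "n=sample size/group", and states the target as an "80% chance (i.e., power) to be 95% confident that the therapy is good value" at a willingness to pay of 80,000 per QALY. The inputs include "W=80,000, C=832,E=0,02". The section names no attrition rate and no inflation of the result.

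Section 3 (Study design) describes a study "designed as a parallel-group randomized controlled trial (N = 156") with 78 allocated to each arm. The flowchart places 156 at the randomisation step. The last EQ-5D and TiC-P assessment, T3, is at weeks 64-72 (Section 3 and Table 1).

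On withdrawal, the protocol says: "Subjects can leave the study at any time for any reason if they wish to do so". The section headed "Replacement of individual subjects after withdrawal" is marked not applicable.

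**The concern.** The formula has no term for missing data. Its n counts patients whose costs and QALYs are available for the comparison. The protocol uses one number for two quantities: the patients needed in the analysis and the patients randomised. They coincide only if practically nobody is lost.

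That is a demanding condition here. QALYs are built from utilities across all follow-up periods, the questionnaires are completed online, and the last assessment falls more than a year after randomisation. If the condition fails, the study has less chance than stated of showing that blended care is good value at the chosen threshold. An inconclusive result would then be more likely than a reader of section 4.4 would expect, even if every planning input were right.

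**Working it through.** **Inputs (section 4.4).** z_alpha = 1.96, z_beta = 0.84, sd_c = 800, sd_e = 0.02, W = 80,000, C = 832, E = 0.02, rho = 0.1. In the printed formula two standard deviations lack a subscript and one carries q. They are read as sd_c and sd_e, with sd_q taken as sd_e.

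**Step 1: reproduce the plan's figure.**

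- Formula: n per group = 2(z_alpha + z_beta)² × [sd_c² + W²sd_e² − 2W·rho·sd_c·sd_e] / (WE − C)²
- Multiplier: 2 × 2.80² = 15.68
- Variance of net benefit: 640,000 + 2,560,000 − 256,000 = 2,944,000, so SD = 1,715.8
- Difference in net benefit: 1,600 − 832 = 768, and 768² = 589,824
- n = 15.68 × 2,944,000 / 589,824 = 78.26 per group

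Taking 78 per group gives 156. The stated total is therefore the formula's own output, with nothing added.

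**Step 2: look for a hidden allowance.** A one-sided z of 1.645 would need 2 × 2.485² × 2,944,000 / 589,824 = 61.6 per group. On that reading, 78 would leave room for about 21% loss (1 − 61.6/78). But the section states 1.96, so 156 cannot be read as containing a margin.

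**Step 3: power of 156 randomised if only completers count.** Power(n) = Phi(768 × √(n/2) / 1,715.8 − 1.96). The protocol gives no loss rate, so a range is assumed.

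| Assumed loss | Completers per group | Power |
| --- | --- | --- |
| 0% | 78 | 79.8% |
| 10% | 70.2 | 75.5% |
| 20% | 62.4 | 70.5% |
| 30% | 54.6 | 64.8% |

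For scale, power is about 79.6% with one patient missing in total and 79.3% with two.

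**Step 4: dependence on C.** The 156 is reproduced only with C = +832. This gives a ratio of 832 / 0.02 = 41,600 per QALY, in line with the roughly 40,000 that section 4.4 mentions. The same section also describes lower costs for the blended arm, and section 2 expects the same. With C = −832 the denominator becomes (1,600 + 832)² = 5,914,624, and n = 15.68 × 2,944,000 / 5,914,624 = 7.8 per group. On that sign, any plausible loss from 78 would be immaterial.

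**The case against.** The strongest objection is that an incomplete patient is not a patient who contributes nothing. Section 10.1 analyses costs with a multilevel model for repeated measurements and extrapolates the TiC-P data to twelve months assuming stable costs. A missed assessment therefore need not remove someone from the analysis. How missing data will be handled may also be set out in a statistical analysis plan that is not at hand. This stands as far as it goes: the completers-only figures are a lower bound on power at each assumed rate, not a forecast. It does not rescue the stated 80%. The sample size calculation does not invoke the model, and a model cannot restore all the information from follow-up that was never observed.

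A second objection is that the sign of C matters far more than attrition. That is correct, and the power figures here are conditional on the sign that yields 156.

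Three stronger readings are tempting, and the documents do not support them:

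- A reader might infer that the power collapses as soon as one patient is lost. One missing patient costs only about 0.2 percentage points; the issue is sizeable attrition.
- A reader might treat the step from 78.26 to 78 as an error worth correcting. It also costs about 0.2 points, which is negligible beside inputs rounded to one or two figures.
- A reader might take the planned process measure, "What is the percentage of dropout during therapy", as an admission that outcome data will be lost. It concerns adherence to treatment. Patients who stop treatment are still asked for the post-test measurement (section 8.6).

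Nor is the absence of replacement a fault in a randomised trial. It only means that nothing offsets whatever loss occurs.

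**Conclusion.** The point holds. Section 4.4 claims 80% power for a number that equals the complete-data requirement, and the protocol makes no allowance for attrition anywhere. With all printed inputs kept, including C = +832, 156 randomised gives 79.8% power only if the cost and QALY data are essentially complete. Under a completers-only analysis the shortfall from 79.8% would be about 4 points at 10% loss, 9 at 20% and 15 at 30%. Those rates are assumed, and use of partial records would make the shortfall smaller. The claim is about the stated power. It does not show that the trial is too small, and the documents give no basis for saying how many patients will be lost.

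**What to change.** In section 4.4:

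1. Reconcile the sign of C with the text that describes lower costs for blended care, since every power figure depends on it.
2. Distinguish the number randomised (156) from the number expected to have complete cost and QALY data, and state that expected proportion with its basis.
3. Restate the power of 156 randomised at that proportion, labelled as completers-only. If C = +832 is confirmed and 20% incomplete is expected, for example, the text would say about 70%, and that use of partial records may raise it.

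The second and third items take two sentences and a lower stated power. They need no extra patients and no change to the design or analysis. The first item takes a decision on which statement about costs was intended, and the calculation must then be rerun.

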# The results of this cost-effectiveness study will provide a) insight into the health-economical outcomes of ‘blended treatment’, b) indication whether blended treatment will add value when it is implemented in clinical settings, and c) insight in whether blended treatment for anxiety is advisable and feasible from the perspective of various stakeholders.2. OBJECTIVES

This cost-effectiveness study will compare blended cognitive behavioral treatment (bCBT) with standard face-to-face CBT (CBT-TAU) among patients with a diagnosis of an anxiety disorder referred to an outpatient specialized mental health care.

The main goal of the study is to explore the health-economic outcomes of bCBT in comparison to CBT-TAU, through cost-effectiveness analysis (CEA), cost-utility analysis (CUA) and a budget impact analysis (BIA), both from a societal and a healthcare perspective.

We assume that bCBT and CBT-TAU are similarly clinically effective, but that bCBT can be offered at lesser costs. Hence, we expect health-economic outcomes of bCBT to be favorable in comparison to those of CBT-TAU. If so, this would justify further large-scale evaluations and dissemination efforts.

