### Main study parameter/endpoint

#### Clinical outcomes

Primary clinical outcomes are 1) severity of anxiety symptoms measured with the Beck Anxiety Inventory (BAI), 2) quality-adjusted life years (QALY’s), derived from the Euro Quality of Life questionnaire (EQ-5D-3L) and health-related quality of life, tapped by the SF-36 Health Survey.

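### The 80% power in section 4.4 holds only if patients' QALYs vary with an SD of about 0.02, an unsourced value equal to the expected difference between arms

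*Protocol*

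**What the plan says.** Section 4.4 of the protocol sizes the trial with a net-benefit formula: "For this study a sample size of 156 is based on a formula" for the power of a cost-effectiveness analysis. The Study Design section splits the total equally, with patients "randomly allocated to either bCBT (n=78) or CBT-TAU (n=78").

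The inputs include "sd}_{e}=0,02$, $W=80,000, C=832,E=0,02", with a cost SD of 800, a correlation of 0.1 and z-values of 1.96 and 0.84. The stated aim is an "80% chance (i.e., power) to be 95% confident that the therapy is good value" at a willingness to pay of at most 80,000 per QALY. The same paragraph describes the scenario as "using only a small increase in quality of life and lower costs for blended eHealth".

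The main endpoint section names "quality-adjusted life years (QALY’s), derived from the Euro Quality of Life questionnaire (EQ-5D-3L"). The protocol gives no other SD for QALYs or for EQ-5D utilities, and it cites nothing for the 0.02.

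**The concern.** The SD in the formula is the spread of QALYs between patients. Here it has the same value as the difference expected between arms, so on the QALY scale the planned effect is one full SD. That is a demanding assumption for a gain that the text presents as small.

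The protocol's own design makes so narrow a spread hard to accept. QALYs accumulate to week 64-72, that is 1.23 to 1.38 years. An SD of 0.02 QALY over that time means that patients' average utilities vary with an SD of only about 0.014 to 0.016. The sample mixes three severe anxiety disorders, scored on an instrument with 243 health states, and the treatment section expects comorbidity and some insufficient responders. As an illustration, suppose half the patients respond and nothing else varies. The SD is then half the gap between responders and non-responders, so 0.02 allows a gap of only 0.04 QALY.

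This is the trial's only power justification, and it concerns its main goal. If the spread is wider, an inconclusive cost-utility result would be read as coming from a trial with 80% power when it had much less.

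**Working it through.** **Inputs (all from section 4.4 unless noted).** z-values 1.96 and 0.84; sd_c = 800; sd_e = 0.02; W = 80,000; C = 832; E = 0.02; rho = 0.1; 78 per arm (Study Design). The printed formula lacks some subscripts. I read the two bare SDs as sd_c and sd_e, and sd_q as sd_e.

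**Reproducing the plan's figure.**

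V = sd_c² + W²·sd_e² − 2·W·rho·sd_c·sd_e = 640,000 + 2,560,000 − 256,000 = 2,944,000

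n per arm = 2(1.96 + 0.84)² × V / (W·E − C)² = 15.68 × 2,944,000 / (1,600 − 832)² = 15.68 × 2,944,000 / 589,824 = 78.26

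Power at 78 per arm = Φ(768 / √(2V/78) − 1.96) = Φ(768/274.75 − 1.96) = Φ(0.835) = 79.8%

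This matches 78 per arm, 156 in total and 80%.

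**Where the result comes from.** The QALY term is 2,560,000 of 3,200,000 before covariance, or 80%. The standardised difference is 0.02/0.02 = 1.0 for the QALY component and 768/√2,944,000 = 768/1,716 = 0.45 on the net-benefit scale, which is the one powered.

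**The sign of C.** Only C = +832 (bCBT dearer) gives 156, and 832/0.02 = 41,600 fits the stated ratio of around 40,000. Yet the text speaks of lower costs for the blended arm. With C = −832 the denominator becomes (1,600 + 832)² = 2,432² and the formula needs about 8 per arm. Both signs are therefore shown.

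**Sensitivity to sd_e.** V is recomputed for each sd_e and all other inputs are kept. Power = Φ(|W·E − C| / √(2V/78) − 1.96). The half-width of the 95% CI for incremental net benefit is 1.96·√(2V/78) and does not depend on C. Every sd_e above 0.02 is my assumption.

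| sd_e | Power, C = +832 | Power, C = −832 | n per arm for 80%, C = +832 | 95% CI half-width (EUR) |
|---|---|---|---|---|
| 0.02 | 79.8% | >99.9% | 78.26 | 539 |
| 0.023 | 70% | >99.9% | 100 | 606 |
| 0.03 | 50% | >99.9% | 160 | 770 |
| 0.05 | 22% | 97% | 426 | 1,255 |
| 0.10 | 9% | 48% | 1,685 | 2,498 |
| 0.20 | 5% | 16% | 6,755 | 5,003 |

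Example at 0.05: V = 640,000 + 16,000,000 − 640,000 = 16,000,000; √(2 × 16,000,000/78) = 640.5; half-width 1.96 × 640.5 = 1,255; power Φ(768/640.5 − 1.96) = Φ(−0.761) = 22%. With C = −832 it is Φ(2,432/640.5 − 1.96) = Φ(1.837) = 97%.

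**The case against.** A reader might infer that the sample size contains an arithmetic error, or that the trial does not have 80% power. The documents support neither. The formula reproduces the stated figures, and no other QALY SD is available in the protocol to prove 0.02 wrong. The loss of power is conditional on SDs that I have assumed. That part of the objection stands.

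It also stands that the size of the loss depends on the sign of C. If bCBT is cheaper by 832, as the wording suggests, power is still about 97% at an SD of 0.05, so the steep fall between 0.02 and 0.05 is not robust. At 0.10 and above, power is low with either sign.

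A reader might also see a contradiction with the wording. The Objectives say "We assume that bCBT and CBT-TAU are similarly clinically effective", and section 4.4 calls the gain small. Both can be read as statements about an absolute gain of 0.02 QALY, so they do not refute the inputs. The standardised difference of 1.0 belongs to one component of the quantity that is powered, not to a test that the protocol plans.

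Finally, the aim is exploratory, and the analysis section plans bootstrapped ratios, an acceptability curve and sensitivity analyses rather than a pass/fail test at 80,000. Those outputs will show the uncertainty. They do not correct the unconditional power claim in section 4.4.

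**Conclusion.** The concern holds as an unsupported design input. The 80% is correct for the stated inputs, but it requires a between-patient QALY SD of about 0.02. That value has no source, equals the expected difference, supplies 80% of the variance before covariance, and is implausibly small for this population, instrument and horizon.

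The claim is fragile. With C = +832, an SD of 0.023 already takes power to about 70%, and 0.03 takes it to about 50%. At an assumed SD of 0.10 power is 9% or 48% depending on the sign of C, and at 0.20 it is 5% or 16%. These figures assume that the cost SD, correlation, willingness to pay, QALY difference and absolute cost difference are as stated, and that all 156 patients contribute data.

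**What to change.** In section 4.4:

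- Replace sd_e with a patient-level SD of EQ-5D QALYs over the trial horizon, and cite its source.
- Reconcile the sign of C with the text. The entry "W=80,000, C=832,E=0,02" yields 156 only if bCBT costs more, whereas the accompanying sentence says it costs less.
- Keep N = 156. Replace the unconditional 80% statement with the recomputed power and a short table, by sd_e, of power and the 95% CI half-width of incremental net benefit at 80,000 per QALY.
- If the recomputed power is low, present the cost-utility result as estimation. Dropping the power statement before the SD is known would be premature.

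The cost is a rewritten paragraph and probably a less favourable stated power. Patient numbers, procedures and data collection do not change.

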**CEA/CUA**

Costs will be assessed at pre-, mid-, post-treatment and at one-year follow up. As the TIC-P cost date covers a period of three months, all costs will be extrapolated to a 12 months period assuming a stability of costs during the time frame. T-tests will test the change for each cost domain. As cost data will not be normally distributed, p-values will be estimated using a multilevel model (with repeated measurements to control for dependency between the measurements) after which a bootstrap analysis on the parameters is performed (10,000 replications, to generate a reliable cost estimate [23]. An incremental cost-effectiveness ratio (costs per case response or remission) and will be calculated (ICER =(mean costs blended eHealth treatment-mean costs TAU)/(mean bCBT -mean CBT-TAU). The mean costs, including all medical and non medical costs, of the patients in the blended eHealth condition will be subtracted from the mean costs of the patients in the TAU condition. This difference will be then be divided with the subtracted effects (case of response or remission on the BAI). This procedure will be bootstrapped 10,000 times, generating an estimation of the blended eHealth treatment groups’ incremental costs in relation to their incremental health benefit. Additionally an incremental cost-utility ratio (costs per QALY) will be calculated; this procedure is identical to the cost-effectiveness ratio with the exception that instead of a case of response or remission, an additional quality adjusted life year is calculated (QALY). Finally, to test the robustness of the results, we will conduct a sensitivity analyses, to investigate how sensitive the ICERs will be to changes of cost estimates (for example difference in costs per iCBT contact, type of psychologists and number of sessions). For decision-making purposes, the ICER acceptability curve will be plotted for various willingness-to-pay (WTP) ceilings, which helps making judgments about whether the blended intervention offers good value for money, relative to treatment as usual. One-way sensitivity analyses directed at uncertainty in the main cost drivers will be performed to gauge the robustness of our findings across a range of likely values of those parameters.

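### Acceptability is stated as an unsigned cost-per-QALY ratio, and section 10.1 gives that ratio's cost difference in two directions, so in the expected cheaper-but-similar case the ratio cannot tell good value from poor

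*Protocol*

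**What the plan says.** Protocol section 4.4 (Sample size calculation) contains two statements about value for money. The first is the design target, "an 80% chance (i.e., power) to be 95% confident" of good value at a willingness to pay of no more than 80,000 per QALY. It is sized with a formula whose denominator is (WE - C) squared, using "W=80,000, C=832,E=0,02". The second closes the paragraph: "a costs-effectiveness ratio between 20.000 and 80.000 Euro per QALY is assumed acceptable". The same paragraph expects that "the point estimate for the cost-effectiveness ratio will be around 40,000 per quality- adjusted life year (QALY") and describes the scenario behind that figure as a small QALY gain together with lower costs for the blended arm.

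Section 2 (Objectives) states the expectation: "We assume that bCBT and CBT-TAU are similarly clinically effective, but that bCBT can be offered at lesser costs".

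Section 10.1 (CEA/CUA) defines the ICER by a formula with both differences as blended minus usual care. The sentence after the formula subtracts the blended arm's costs from the usual-care arm's costs, which is the reverse. The procedure of dividing the cost difference by the effect difference is then bootstrapped 10,000 times. The cost-utility ratio follows the identical procedure with QALYs as the effect. For decision-making, "the ICER acceptability curve will be plotted for various willingness-to-pay (WTP) ceilings".

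**The concern.** Comparing a ratio with a ceiling works when the new treatment costs more and gains health. It does not carry over to the other quadrants. If the treatment is cheaper and better, the ratio is negative and its size says nothing about value. If it is cheaper and worse, the ratio is positive and the comparison reverses: the saving per QALY lost must exceed the ceiling. The trial expects lower cost and a QALY difference near zero, so its results should straddle exactly these two quadrants.

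The cost difference is also written in both directions, so the sign of the reported ratio is not fixed. Section 4.4 already shows the confusion: a QALY gain at lower cost is paired with a positive ratio near 40,000, whereas the formula in 10.1 makes that ratio negative. At stake is whether the primary result is read correctly, because opposite conclusions can carry the same number.

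**Working it through.** **Inputs, all from section 4.4:** z values 1.96 and 0.84; SD of costs 800; SD of effects 0.02; W = 80,000; C = 832; E = 0.02; "correlation between differences in costs and effects" 0.1. Section 3 gives 78 per arm.

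**1. Reproduce the sample size.**
- Variance term: 800² + 80,000² × 0.02² - 2 × 80,000 × 0.1 × 800 × 0.02 = 640,000 + 2,560,000 - 256,000 = 2,944,000.
- Denominator: (80,000 × 0.02 - 832)² = 768² = 589,824.
- n per arm = 2 × 2.8² × 2,944,000 / 589,824 = 78.26, against the stated 78. The plan's figure is reproduced.
- With the sign that lower costs would imply (C = -832), the denominator is (1,600 + 832)² = 2,432² and n = 7.8 per arm. The stated 78 therefore comes out only with blended care costing 832 more.

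**2. Ratio against net benefit.** Differences are bCBT minus CBT-TAU. Net benefit = W × QALY difference - cost difference. The last column uses the cost subtraction as worded in 10.1.

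| QALY diff. | Cost diff. | Ratio | In 20,000-80,000? | Net benefit, W = 80,000 | Net benefit, W = 20,000 | Ratio, cost reversed |
|---|---|---|---|---|---|---|
| +0.02 | +832 | +41,600 | yes | +768 | -432 | -41,600 |
| +0.02 | -832 | -41,600 | no | +2,432 | +1,232 | +41,600 |
| -0.02 | -832 | +41,600 | yes | -768 | +432 | -41,600 |
| -0.02 | +832 | -41,600 | no | -2,432 | -1,232 | +41,600 |

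Rows 1 and 3 share a ratio but have opposite net benefit at each W. Rows 2 and 4, the best and worst results, share the other ratio. Reversing the cost subtraction swaps which pair is positive and resolves neither.

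The lower end of the range does not work as a floor either. A gain of 0.02 at an assumed extra cost of 200 gives a ratio of 10,000, outside the range, with net benefit at 80,000 of 1,600 - 200 = +1,400.

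**3. How often this would matter.** One million simulated trials used 78 per arm, the plan's SDs and correlation, and W = 80,000. The standard errors are 800 × √(2/78) = 128.1 for cost and 0.02 × √(2/78) = 0.0032 for QALYs. Treating 832 as a saving is an assumption made for illustration.
- No true QALY difference, saving of 832: 50.0% of point estimates are dominant and none of those lies in the range. In all, 0.12% lie in the range, while net benefit is positive in 99.9%. Check: the SE of net benefit is √(2,944,000 × 2/78) = 275, and 832/275 = 3.03.
- True loss of 0.02 QALY, saving of 832: 99.7% lie in the range, while net benefit is positive in 0.3%. Check: -768/275 = -2.80.

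**The case against.** The range is not the trial's decision rule. The sentence before it sets the operative target, "to be 95% confident that the therapy is good value when we are willing to pay at most 80,000 per QALY", and the formula behind it is signed net benefit, which judges every row of the table correctly. The range sentence speaks of Dutch practice and reads as background for choosing W. This stands. A reader might infer that the range is the only pass mark, and the document does not support that. But the signed criterion appears only where the trial is sized; section 10 names no net benefit, quadrant or signed rule.

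A reader might also infer that the acceptability curve will be the share of replicates with a ratio at or below each ceiling. Section 10.1 does not say so. A net-benefit curve fits its words equally well, and a statistical analysis plan that is not shown may settle it. That omission alone is no fault. What the protocol does write down, however, is a bootstrapped ratio whose cost difference runs both ways.

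Finally, a reader might infer that a health-losing treatment would usually pass in the scenario the trial expects. It would not. With no QALY difference and a saving of 832, only about 0.1% of estimates enter the range. A loss of 0.005 with that saving gives 166,400, outside it, with net benefit at 80,000 of -400 + 832 = +432. The 99.7% figure needs a true loss of 0.02, a full SD on the plan's inputs. Nor is that loss poor value at every ceiling, since net benefit is +432 at 20,000.

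**Conclusion.** The concern holds in a limited form. The ratio range in 4.4 lacks a sign and a quadrant, section 10.1 contradicts itself on the direction of the cost difference, and the signed rule used for sizing is not carried into the analysis. In the quadrants the trial expects, the ratio alone then cannot separate good value from poor: results with net benefits of +2,432 and -768 have ratios of -41,600 and +41,600, and the larger benefit is the one outside the stated range. The firmer half is that a dominant result falls outside the range; the health-losing case inside it is real but needs a QALY loss well beyond similar effectiveness.

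The table needs only the plan's own magnitudes. The percentages further assume normal sampling, the stated SDs and correlation, and a saving of 832. The protocol does not establish that saving, because 832 reproduces its sample size only as an extra cost. The contradiction between lower costs and C = 832 (about 8 against 78 per arm) does not depend on any of these assumptions.

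**What to change.** In section 10.1:
- Take both differences as bCBT minus CBT-TAU, and correct the sentence that reverses the cost subtraction.
- Define good value at W as W × QALY difference - cost difference > 0.
- Compute the acceptability curve at each W as the share of bootstrap replicates meeting that inequality.
- Report the share of replicates in each quadrant beside the ICER.

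In section 4.4:
- State the 20,000 to 80,000 range as willingness-to-pay values for W, not as a range that the ratio must fall in.
- Reconcile the stated lower costs with C = 832 and the positive ratio of about 40,000, and restate the sample size on whichever sign is meant.

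The section 10.1 changes cost a few sentences and one line of code on replicates already planned, with no new data or patients. The rule matches the (WE - C) formula the trial was sized on. Reconciling C needs a decision by the sponsor and may change the stated basis for 156 participants.
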